#### **Follow up at Day 3/4, T48 to T60 hours**

EEG-related findings and changes in clinical trial management will be collected from medical charts

#### **Follow up at Week 4**

Several outcome findings (see detailed study flow chart and 9.2) will be collected from medical chart if the patient is still hospitalized at site or by phone to the patient, representative or general practitioner, depending on the patient’s medical condition, consent status and location.

#### **Follow up at Month 6**

Several outcome findings (see detailed study flow chart and 9.2) will be collected through a structured phone interview (to the patient, representative or general practitioner, depending on the patient’s medical condition, consent status and location) by a study team member delegated by the principal investigator, blinded to the EEG intervention and centralized for all trial sites.

## 10. SAFETY

### 10.1 Interventions studies

As already stipulated under 3.7, since the EEG is a noninvasive procedure, there are no significant risks that will be associated with either rEEG or cEEG. The only potentially challenging issue is a skin reaction under the electrodes in patients undergoing cEEG, which is extremely uncommon before seven to ten days of uninterrupted recording. The participating centers, however, are currently already recording each year many cEEG in the proposed clinical setting, and skin reactions virtually never represent a problem for patients, and may be easily treated with local applications.

#### 10.1.1. Definition, assessment and reporting of (serious) adverse events and other safety related events

An Adverse Event (AE) is any untoward medical occurrence in a patient or a clinical investigation participant administered a pharmaceutical product and which does not necessarily have a causal relationship with the study procedure. An AE can therefore be any unfavourable and unintended sign (including an abnormal laboratory finding), symptom, or disease temporally associated with the use of a medicinal (investigational) product, whether or not related to the medicinal (investigational) product (ICH E6 1.2).

As per ClinO Art.63, a Serious Adverse event (SAE) is defined as any event that :

- a. requires inpatient treatment not envisaged in the protocol or extends a current hospital stay;
- b. results in permanent or significant incapacity or disability;
- c. is life-threatening or results in death; or
- d. causes a congenital anomaly or birth defect.

**During the intervention phase of the study, all serious adverse events (SAEs) that cannot be excluded to be attributable to the intervention under investigation, will be collected,** fully investigated and documented in source documents and case report forms (CRF). It is not expected to experience SAE related to the intervention occurring after the intervention.

Additionally, all these events will be reported by the local investigator to the sponsor-coordinating investigator as soon as possible (within 24h). The sponsor-coordinating investigator will report these events to the lead CEC within 15 days (ClinO Art. 63).

If immediate safety and protective measures have to be taken during the conduct of the clinical trial, the local investigator will inform the sponsor-coordinating investigator as soon as possible. The latter will notify the lead CEC of these measures, and of the circumstances necessitating them, within 7 days (ClinO Art.37).

Once a year, the sponsor-coordinating investigator will submit to the lead CEC an annual safety report summarising the safety of participants (ClinO Art.43).

#### 10.1.2. Follow up of (Serious) Adverse Events

SAEs that cannot be excluded to be attributable to the intervention under investigation will be followed until resolution or stabilisation. Participants with ongoing SAEs at study termination (very improbable) will be further followed up until recovery or until stabilisation of the disease after termination.

## 11. STATISTICAL METHODS

### 11.1 Hypothesis

The null hypothesis is that cEEG, will not improve patients' survival (reduce mortality) at 6 months as compared to rEEG.

### 11.2 Determination of Sample Size

According to the only available study broadly addressing this issue , patients with consciousness disorders and cEEG have a 25% mortality (corresponding to 75% survival rate) and patients without cEEG a 39% mortality (implying a 61% survival rate). Considering a power of 0.8, an alpha error of 0.05, and applying a 2-sided test, 2x174 patients (348 in total) would be needed to detect a difference of 61% versus 75% in survival ( $\chi^2$  test for independent samples, Stata version 12, College station, TX). This represents a reasonable difference of non-debatable clinical relevance.

### 11.3 Statistical criteria of termination of trial

There are no stopping rules for individual participants. The discontinuation criteria for patients are the post hoc or proxy consent refusal/withdrawal, only. An interim analysis of the primary outcome will be performed after recruitment of the first 100 patients if the difference of 14% in survival at six months between the two arms will be met, the study will be interrupted.

### 11.4 Planned Analyses

#### Analysis of the outcomes

All analyses will be carried out by a professional statistician. At study completion, the two interventional groups will be compared regarding survival at six months as "intention to monitor" (predefined analysis for the primary endpoint) and "per protocol", adjusted for potential confounders (logistic regressions).

Analysis of each secondary endpoint will be also conducted using univariate and multivariate approaches.

For univariate approaches, frequency tables ( $\chi^2$  or Fisher exact tests, as needed), t-test, Mann-Whitney U, and Kaplan-Meier tests will be applied, as needed.

For the multivariate approaches, stepwise logistic regression models will be performed to identify independent outcome predictors among those found to have a  $p < 0.1$  on univariate analyses. Accordingly, risk-prediction models will be set-up and "Goodness-of-fit" of these models will be evaluated using a Hosmer-Lemeshow test to ensure the quality of calibration. Solid predictors will be used to predict survival and functional outcome at six months in a model. To evaluate the performance of these models, sensitivity, specificity, positive predictive value, negative predictive value, unweighted accuracy (using exact binomial 95% CI), area under the Receiver Operating Characteristic (ROC) curve, and reclassification analysis (Net Reclassification Improvement – NRI) will be calculated .

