| Eligibility check and inclusion                                                       | X              |                     |           |          |                 |                   |
| Estimated body weight                                                                 | X              |                     |           |          |                 |                   |
| Charlson Comorbidity Index (CCI)                                                      | X              |                     |           |          |                 |                   |
| Modified Ranking Scale (mRS)
*extrapolated before current hospitalization   | X*             |                     |           |          | X        | X          |
| SAPS II (only if available)                                                           | X              |                     |           |          |                 |                   |
| Laboratory (only if available)                                                        | X              |                     |           |          |                 |                   |
| Randomization                                                                         | X              |                     |           |          |                 |                   |
| EEG(s) details (Dates/times, electrodes numbers, use of interpretation algorithms)    |                       | X            |           |          |                 |                   |
| Detection of seizures (time, clinical correlate) and/or SE (time, type, STRESS score) |                       | X            |           |          |                 |                   |
| Interictal epileptiform features (after ACNS)                                         |                       | X            |           |          |                 |                   |
| EEGs description                                                                      |                       | X            |           |          |                 |                   |
| Medication during EEG (except fluids, vitamins and feeding)                           |                       | X            |           |          |                 |                   |

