### **5.2 Secondary Outcomes**

- Functional outcome at four weeks and at six months (evaluated using the modified Rankin Scale (mRS), and the Cerebral Performance Categories (CPC) , ordinal),
- Evaluation at 4 weeks and 6 months of the ability to go back to work/school if previously working/at school (proportion),
- Seizure/SE detection rate, and time to detection after the start of EEG recording, and presence of concomitant clinical signs of seizures (proportion, resp. continuous variable)
- Detection of interictal potentially epileptiform features (spikes, spike and waves, sharp waves, isolated or repeated at <3Hz without any evolution; lateralized rhythmic delta activity  (proportion),
- Rate of in-hospital infections requiring antibiotic treatment at 4 weeks after first EEG (proportion),
- Need and duration of mechanical ventilation at 4 weeks after first EEG (proportion, resp. continuous variable),
- Duration if ICU and hospital stay (continuous variable),
- Patient destination after acute facility (home, rehab, nursing home, other; categorical)
- Change in clinical patient management (i.e., antiepileptic drugs (AED) introduced or stopped, AED increased or decreased, brain imaging procedure order) occurring during the 60 hours following the start of the first EEG (categorical).
- Correlation between quantitative EEG analysis and outcome.

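### Pre-hospital mRS is collected at inclusion, but section 11.4 does not prespecify its use when the arms are compared on mRS at 4 weeks and 6 months

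*Protocol*

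**What the plan says.** - **Baseline.** The Study Schedule, repeated in section 9.1, lists an mRS assessment at screening/inclusion, marked as "extrapolated before current hospitalization". CPC has no baseline entry.
- **Outcome.** Section 5.2 lists first among the secondary outcomes "Functional outcome at four weeks and at six months (evaluated using the modified Rankin Scale (mRS), and the Cerebral Performance Categories (CPC", and labels it ordinal.
- **Analysis.** Section 11.4 says "Analysis of each secondary endpoint will be also conducted using univariate and multivariate approaches"; the synopsis says the same. For the univariate part, besides chi-square or Fisher tests, "t-test, Mann-Whitney U, and Kaplan-Meier tests will be applied, as needed". For the multivariate part, "stepwise logistic regression models will be performed to identify independent outcome predictors among those found to have a" univariate p below 0.1.
- **Adjustment of the primary endpoint.** The survival comparison is "adjusted for potential confounders (logistic regressions"; no confounder is named.
- **Design.** Section 6.2.1 stratifies the 1:1 randomization by center only. Section 7.1 sets no limit on prior disability.

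Section 11 does not mention pre-hospital mRS as a covariate, a stratum or a change score. It does not exclude it either.

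**The concern.** The baseline value of an outcome measured on the same scale is usually one of its strongest predictors. Here it is collected, and the population is likely to vary widely in prior disability: any etiology, intensive or intermediate care, no upper limit on pre-hospital mRS. If the arm comparison ignores it, that variation stays in the error term, and any chance imbalance in prior disability carries into the functional result. The synopsis objective is framed in terms of better functional outcome, so this comparison will be read closely although it is secondary.

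The multivariate layer does not settle the matter. Its stated purpose is to find outcome predictors and build risk-prediction models, not to estimate a baseline-adjusted arm effect. Entry depends on the data, and read literally this applies to the arm term too. Ordinary logistic regression also needs a binary outcome, whereas section 5.2 declares mRS ordinal and gives no cut.

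**Working it through.** **1. The plan's own figure.** Section 11.2: "Considering a power of 0.8, an alpha error of 0.05, and applying a 2-sided test, 2x174 patients (348 in total) would be needed" for survival of 61% versus 75%. With pooled variance and no continuity correction, mean proportion 0.68:

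n = [1.960·√(2·0.68·0.32) + 0.842·√(0.61·0.39 + 0.75·0.25)]² / 0.14² = (1.293 + 0.549)² / 0.0196 ≈ 173.1, so 174 per arm.

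The figure reproduces. It concerns mortality and is not affected by this point. The protocol states no power for mRS.

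**2. Gain from adjustment.** Inputs: 174 per arm and two-sided alpha 0.05 (section 11.2). Assumed: an effect that the unadjusted test detects with 80% power, and a correlation r between pre-hospital and follow-up mRS. The effect is (1.960 + 0.842)·√(2/174) = 0.300 SD. Adjustment multiplies the residual variance by 1 − r², so

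power = Φ(2.802/√(1 − r²) − 1.960), equivalent n per arm = 174/(1 − r²).

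| r (assumed) | Residual variance | Power | Equivalent n per arm |
|---|---|---|---|
| 0.1 | −1% | 80.4% | 176 |
| 0.2 | −4% | 81.6% | 181 |
| 0.3 | −9% | 83.6% | 191 |
| 0.4 | −16% | 86.4% | 207 |
| 0.5 | −25% | 89.9% | 232 |

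**3. Check on an ordinal scale.** Simulation with 174 per arm and 3,000 runs per setting. Assumed: a 7-level follow-up mRS with 32% in the worst level (the mean of 39% and 25% mortality in section 11.2), a 6-level pre-hospital mRS, and a latent shift of 0.31 SD. Mann-Whitney is compared with rank ANCOVA on pre-hospital mRS.

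| Observed rank correlation | Unadjusted power | Adjusted power |
|---|---|---|
| 0.17 | 78.4% | 79.8% |
| 0.26 | 79.9% | 82.3% |
| 0.34 | 77.4% | 83.3% |
| 0.44 | 78.3% | 85.6% |

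The Monte Carlo standard error of each power is about 0.8 points (√(0.78·0.22/3000)), so the pattern agrees with step 2.

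**4. Validity without adjustment.** With no effect, Mann-Whitney rejected in 4.8% to 5.2% of simulated trials at every correlation tried. Leaving the baseline out does not inflate type I error.

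**5. Chance imbalance.** The standard error of the baseline difference between arms is √(2/174) = 0.107 SD. An imbalance of that size moves the unadjusted outcome difference by r·0.107. At r = 0.4 this is 0.043 SD, or 14% of the 0.300 SD effect.

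**The case against.** The strongest reply is that the univariate tests are only half of the plan. Each secondary endpoint also gets a multivariate analysis, and pre-hospital mRS could enter it. In a simulation under similar assumed distributions with the outcome dichotomised, it passed the p<0.1 screen in about 99% of trials at an observed correlation of 0.26, in all of them at 0.34 and above, and failed in about 15% near 0.17, where little is gained. So a reader who infers that the protocol does not use the baseline at all goes too far. What remains is that passing the screen is not retention after stepwise selection, that the arm term has no protected place, and that a logistic model on an unstated cut is not an ordinal comparison.

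A reader might also infer that uncounted prior disability biases the result, or that a patient who returns to a pre-hospital mRS of 3 or 4 is misclassified as a poor outcome. The documents support neither. Randomization balances prior disability in expectation, and no good/poor cut is defined; adjustment would not change any patient's score.

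It is also fair that covariate lists are often left to a statistical analysis plan. But section 11.4 does more than stay silent: it fixes a data-driven selection rule. Finally, the score may be unobtainable when no relative can be reached (section 2.7 foresees this) within a screening period of at most 5 hours. That stands, and the fix needs a missing-value rule.

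**Conclusion.** The point holds as a modest matter of efficiency and prespecification. Section 11.4 does not commit to a baseline-adjusted arm comparison of the ordinal mRS, although the baseline is collected. The gain from doing so is about 2 to 10 power points for correlations of 0.2 to 0.5 and negligible below 0.2. These figures rest on an assumed correlation, an assumed 80% starting power and, in the simulation, assumed mRS distributions; the protocol supplies none of them. They compare adjustment with the unadjusted tests, so the gain is smaller in trials where the stepwise model would have kept both arm and baseline mRS. The primary endpoint and its sample size are not affected, and no bias between arms is expected.

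**What to change.** In section 11.4, state that:

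- the main between-arm comparison of mRS at 4 weeks and at 6 months is one prespecified ordinal model (for example proportional odds, or rank ANCOVA) with arm, pre-hospital mRS and center as fixed terms, none of them subject to stepwise selection;
- CPC is analysed in the same way with pre-hospital mRS as covariate, as it has no baseline of its own;
- patients with a missing pre-hospital mRS stay in the analysis by a simple rule, such as a missing indicator or single imputation;
- the unadjusted Mann-Whitney test is supportive.

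The stepwise models can remain for their prognostic purpose. The cost is a few lines of wording, with no new data, visits or patients. The small downside is that an extrapolated score carries measurement error and will sometimes be missing; this reduces the gain but does not bias the randomised comparison.

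### The adjusted analysis of mRS and CPC does not match their declared ordinal scale: the only multivariable model named is stepwise logistic regression, with no cut-point and no guarantee that trial arm stays in the model

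*Protocol*

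**What the plan says.** Section 5.2 lists functional outcome first among the secondary outcomes: "Functional outcome at four weeks and at six months (evaluated using the modified Rankin Scale (mRS), and the Cerebral Performance Categories (CPC", and gives its scale: "Cerebral Performance Categories (CPC) 32 , ordinal". Section 9.2.2 repeats this for both 4 weeks and 6 months. Neither section gives a cut-point.

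Section 11.4 (Analysis of the outcomes) then says:

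- **Scope:** "Analysis of each secondary endpoint will be also conducted using univariate and multivariate approaches".
- **Unadjusted tests:** frequency-table tests, and "t-test, Mann-Whitney U, and Kaplan-Meier tests will be applied, as needed".
- **Adjusted method:** "For the multivariate approaches, stepwise logistic regression models will be performed to identify independent outcome predictors", with candidates limited to those reaching p<0.1 on univariate analysis.
- **Use of the models:** "Solid predictors will be used to predict survival and functional outcome at six months in a model".
- **How the models are judged:** a Hosmer-Lemeshow test; then "To evaluate the performance of these models, sensitivity, specificity, positive predictive value, negative predictive value, unweighted accuracy"; then ROC area and net reclassification improvement.

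No ordinal regression model is named anywhere in the protocol.

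**The concern.** Two features of the adjusted analysis do not fit the endpoint.

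**Scale.** Sensitivity, specificity and predictive values need a two-category outcome. A stepwise logistic model of mRS or CPC judged that way needs a good/poor cut, and the protocol has none. If the cut is chosen later, the result can depend on where it falls. The treating teams and electroencephalographers are not blinded to allocation, so this is discretion better removed in advance.

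**Model building.** The model keeps whatever passes a p<0.1 screen and stepwise selection. Nothing forces trial arm in. If cEEG had no effect, arm would fail that screen in about 90% of trials (1 − 0.10), leaving no adjusted treatment estimate to report.

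The synopsis states its objective in terms of functional outcome, Section 4.3 names it among the secondary objectives, and the 6-month assessment is blinded and centralised. The adjusted result should use the scale that is collected.

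**Working it through.** **1. The texts side by side**

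| Element | Protocol | Scale |
|---|---|---|
| Endpoint (5.2, 9.2.2) | mRS and CPC at 4 weeks and 6 months | ordinal |
| Unadjusted comparison (11.4) | Mann-Whitney U available | ordinal |
| Adjusted analysis (11.4) | stepwise logistic regression | binary as judged; cut not stated |
| Trial arm in adjusted model | not forced in | – |

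The mismatch is confined to the adjusted row.

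**2. The plan's own figure**

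Section 11.2: survival 61% vs 75%, two-sided alpha 0.05, power 0.80.

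n = [1.96·√(2·0.68·0.32) + 0.8416·√(0.61·0.39 + 0.75·0.25)]² / 0.14² = (1.293 + 0.549)² / 0.0196 ≈ 173.1, so **174 per arm**. The stated figure reproduces, with power 80.2%. It concerns mortality only. The odds ratio it implies is (0.75/0.25)/(0.61/0.39) = 1.918.

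**3. What a cut could cost under a common shift**

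Assumptions, none of them in the protocol except the 39% control mortality (11.2) and the 1.918:

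- mRS has seven levels (0–6) and CPC five, with death the worst level of each.
- Control mRS distributions in %: A 3/7/10/12/14/15/39; B 2/4/6/9/15/25/39; C 10/13/12/10/8/8/39.
- Control CPC distributions in %: A 18/13/20/10/39; B 35/13/9/4/39.
- Common odds ratios 1.4, 1.6 and 1.918; n = 174 per arm.

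Ordinal power (Whitehead): V = (2n/12)(1 − Σ p̄ₖ³), power = Φ(ln OR·√V − 1.96). Dichotomised power: two-proportion normal test with pooled variance under the null.

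Worked case, mRS A at odds ratio 1.6: Σ p̄ₖ³ ≈ 0.049, so V = 29 × 0.951 ≈ 27.6 and power = Φ(0.470 × 5.25 − 1.96) ≈ 69.4%. Cut at mRS 0–2: 20.0% vs 28.6%, power 46.2%. Cut at mRS 0–3: 32.0% vs 43.0%, power 56.0%. The losses are about 23 and 13 points.

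| Assumed scale | OR | Ordinal | mRS 0–2 | mRS 0–3 | CPC 1–2 |
|---|---|---|---|---|---|
| mRS A | 1.4 | 42.2% | 25.9% | 32.2% | – |
| mRS A | 1.6 | 69.4% | 46.2% | 56.0% | – |
| mRS A | 1.918 | 92.9% | 75.1% | 84.0% | – |
| mRS B | 1.4 | 41.8% | 19.0% | 26.6% | – |
| mRS B | 1.6 | 69.0% | 33.9% | 47.3% | – |
| mRS B | 1.918 | 92.7% | 59.6% | 76.4% | – |
| mRS C | 1.4 | 42.2% | 33.2% | 34.6% | – |
| mRS C | 1.6 | 69.5% | 57.3% | 58.8% | – |
| mRS C | 1.918 | 92.9% | 84.9% | 85.5% | – |
| CPC A | 1.4 | 41.8% | – | – | 31.9% |
| CPC A | 1.6 | 68.9% | – | – | 55.5% |
| CPC A | 1.918 | 92.6% | – | – | 83.7% |
| CPC B | 1.4 | 40.3% | – | – | 34.6% |
| CPC B | 1.6 | 66.6% | – | – | 58.6% |
| CPC B | 1.918 | 91.0% | – | – | 85.1% |

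The loss is about 8–35 points at mRS 0–2, 7–22 at mRS 0–3 and 6–13 at CPC 1–2. Simulated Mann-Whitney power (4,000 trials per case, at odds ratios 1.6 and 1.918) agrees with the formula to within about 1.5 points.

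**4. When the effect is not a common shift**

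- 8–10 points moved across a single cut (mRS 0–3 or CPC 1–2): Mann-Whitney about 6–8%, dichotomy at that cut 32–57%.
- 14 points moved from death to the worst surviving category: Mann-Whitney 18–32%, alive/dead about 80%.

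The advantage reverses. Steps 3 and 4 compare unadjusted tests. They show what a cut does to the information in the scale; they do not simulate the adjusted model.

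**The case against.** **A reader might infer that the plan dichotomises the functional result outright.** It does not say so. Mann-Whitney U is listed for secondary endpoints, keeps the whole scale, and allows an ordinal unadjusted comparison of the arms. The dichotomy is implied only for the adjusted and prediction models.

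**A reader might also infer a fixed price, such as 10 to 20 points of power.** The documents supply no functional distribution, effect size or power from which to derive one. The ordinal power in such a comparison belongs to a test the plan already names, so the loss cannot be charged to the plan as a whole. Step 4 shows that even its direction depends on the shape of the effect.

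**The performance measures belong to risk-prediction models, not to the between-arm test.** This stands in part: they show a binary target for the functional prediction model and do not by themselves fix the treatment comparison. But no other multivariable method is offered for a comparison promised for each secondary endpoint.

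**Logistic regression could mean ordinal logistic, and model detail belongs in a statistical analysis plan.** Ordinal logistic is a possible reading, but it fits badly with sensitivity, specificity and predictive values. A separate plan, not shown here, might supply the cut. The protocol has nevertheless already fixed a method and a selection rule that do not suit the declared scale, which is more than leaving detail open.

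**Conclusion.** The point holds for the adjusted functional analysis. Section 11.4 pairs ordinal endpoints with stepwise logistic regression judged by binary measures, states no cut, and does not secure trial arm in the model.

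The size is not a single number. Under the assumed distributions, a common odds ratio of 1.4 to 1.918 and 174 per arm, dichotomising costs roughly 6 to 35 points of power depending on scale, cut and effect. Under an effect at one boundary, a cut at that boundary wins. That reversal is no defence of an unstated cut; it shows how far the answer can turn on where the cut is placed.

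The weight is modest. Functional outcome is secondary, the trial is sized on survival alone, and the unadjusted comparison can already be ordinal. This is a free improvement to a secondary analysis.

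**What to change.** In Section 11.4, for mRS and CPC at 4 weeks and 6 months:

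- Make the adjusted between-arm comparison a proportional-odds (ordinal logistic) model with trial arm forced in, centre (the stratification factor in Section 6.2.1) and a fixed list of baseline covariates. Include pre-admission mRS, which the Section 9.1 schedule already collects. Apply no p-value screening to this model.
- Report the common odds ratio with its 95% confidence interval, and describe how the proportional-odds assumption will be examined.
- State in advance the cut for any supportive dichotomy and for the functional prediction model.
- Keep stepwise selection, if wanted, for the prediction models only, labelled as separate from the treatment comparison.

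The cost is a few sentences. It needs no further patients, visits or data. The one thing added is the proportional-odds assumption, which is why it should be described and a pre-stated dichotomy kept alongside.

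### Protocol 11.4 relies on a Hosmer-Lemeshow test alone to assure calibration of the secondary prediction models, which non-rejection in about 348 patients cannot do

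*Protocol*

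**What the plan says.** Under Analysis of the outcomes, Protocol 11.4 says that "stepwise logistic regression models will be performed to identify independent outcome predictors among those found to have a" univariate p-value below 0.1. Risk-prediction models are then built, and their fit "will be evaluated using a Hosmer-Lemeshow test to ensure the quality of calibration". On their use: "Solid predictors will be used to predict survival and functional outcome at six months in a model".

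The other performance measures are sensitivity, specificity, predictive values, accuracy, and "area under the Receiver Operating Characteristic (ROC) curve, and reclassification analysis (Net Reclassification Improvement – NRI) will be calculated". These describe discrimination, classification or reclassification. Hosmer-Lemeshow is therefore the only calibration check named. The protocol gives it no group count, significance level or decision rule.

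The sample size in 11.2 rests on the comparison of the arms: "2x174 patients (348 in total) would be needed to detect a difference of 61% versus 75% in survival".

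**The concern.** The null hypothesis of the Hosmer-Lemeshow test is that predicted and observed risks agree. Rejection is evidence of misfit. Non-rejection is only absence of evidence, and its weight depends on power. The section attaches no estimate, interval or tolerance to calibration, so the stated purpose could be met only through non-rejection.

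At stake is the credibility of the prognostic models. A model that misstates risk in part of its range could be reported as well calibrated because a test with little power against that misfit did not reject.

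**Working it through.** **Inputs.** From Protocol 11.2: 348 patients, two-sided alpha 0.05, power 0.8. cEEG patients "have a 25% mortality (corresponding to 75% survival rate"); those "without cEEG a 39% mortality (implying a 61% survival rate"). With 1:1 allocation (6.2.1), pooled mortality is (25% + 39%)/2 = 32%, or 0.32 × 348 ≈ 111 deaths. Loss of 1-2% (11.4.1) leaves about 341-345 patients, which changes little. Assumptions: ten groups, alpha 0.05, 8 df, binary outcome.

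**1. The plan's own figure.** n per arm = [1.960 √(2 × 0.68 × 0.32) + 0.842 √(0.61 × 0.39 + 0.75 × 0.25)]² / 0.14² ≈ 173.1, rounded up to 174. The stated 2 × 174 reproduces exactly (uncorrected test, power 0.802).

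**2. Miss rate by number of risk groups off by 10 points.** Noncentral chi-square approximation: ncp = k × 34.8 × 0.10² / (0.32 × 0.68) = 1.60k, where k is the number of groups off. The simulations refitted a logistic model to N = 348, 3,000 runs per scenario.

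| Groups off (k) | ncp | Missed, approximation | Missed, simulation |
|---|---|---|---|
| 1 | 1.60 | 89% | 90-91% |
| 2 | 3.20 | 81% | 81-82% |
| 4 | 6.40 | 62% | not run |
| 6 | 9.60 | 43% | not run |
| 10 | 15.99 | 17% | 8-9% (alternating signs) |

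A uniform 10-point shift against fixed predictions (10 df, 5,000 runs) is missed 7% of the time. With a correct model the test rejects in 4.7-5.4%, so its size is right.

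**3. Sensitivity to the risk in the affected groups.** For one and two groups off, the approximate miss rates are 77% and 54% at a risk of 10%, 86% and 74% at 20%, and 90% and 83% at 50%. The 80-90% range thus applies near the pooled risk or above it, and low-risk groups do somewhat better.

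**4. Smooth curvature, one predictor.** Here risk deciles and predictor deciles coincide. An omitted quadratic term is missed 83-86% of the time when the misfit peaks at about 5-7 points, and 33-53% when it peaks at about 9-14 points.

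**5. Smooth curvature, two predictors.** Model: logit = a + 0.6·x1 + 0.6·x2 + 0.3·(x1² − 1), tuned to 32% mortality and fitted without the quadratic term (2,000 trials; the effect sizes are assumptions).

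- True minus predicted risk is 11-12 points in the lowest and highest decile of x1.
- By decile of predicted risk it is +4.7, +1.1, −0.6, −1.8, −2.5, −2.9, −2.6, −1.7, +0.5 and +5.7 points: largest 5.7, mean absolute value 24.1/10 = 2.4.
- Hosmer-Lemeshow rejects in 14.5% of trials (13.8-15.5% in repeat runs), so it misses about 85%.
- A 1-df likelihood-ratio test of x1² detects the curvature in 85% of trials.

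The test pools patients by predicted risk. That dilutes an error concentrated at the extremes of one predictor.

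**6. Would a pass/fail tolerance on a calibration curve do better?** Take the rule that the 95% band must stay within 10 points over the central 90% of predicted risks. With a correct model at N = 348, it was met in 0 of 1,500 simulated trials, with a median maximum half-width of 11.9 points. Such a rule would almost never call any model calibrated.

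**The case against.** The strongest reply has four parts.

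- **The decision rule is inferred.** A reader might conclude that the protocol takes a non-significant result as proof of calibration. It does not say so. It states a purpose, with no threshold or consequence, and a statistical analysis plan that is not shown may add plots or slopes. This stands. What remains is that the protocol itself chose the tool and gave it a purpose it cannot serve.
- **A single miss rate would mislead.** A reader might infer that the test misses a 10-point misfit about 85% of the time whatever its form. The figures do not support that: the rate runs from about 7% to 91% with the pattern of misfit. In the two-predictor scenario no risk decile is off by 10 points. This stands too, and each figure must be tied to its pattern. The 7% case is the less relevant one, because a logistic model with an intercept reproduces overall mortality in the patients it was fitted to, which leaves local misfit as the concern.
- **The curvature comparison is favourable by design.** The likelihood-ratio test targets exactly the term that was planted. Also, the protocol does not say how continuous predictors enter the models, so linear entry is an assumption. Both are fair. The result shows only that the signal was in the data.
- **The consequence is small.** These are secondary prognostic models, and sizing a trial on its primary outcome is no error. This stands and sets the weight of the point.

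**Conclusion.** The concern holds in limited form. Hosmer-Lemeshow is the only calibration check named, and non-rejection with 348 patients and about 111 deaths cannot assure calibration. A 10-point error in one or two of ten risk groups is missed about 80-90% of the time near the pooled risk, less often in low-risk groups. Curvature that leaves 11-12 points of error at the extremes of one predictor, at most about 6 points by risk decile, is missed about 85% of the time. Misfit spread over all groups is usually detected.

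These figures assume ten groups, alpha 0.05, the planning mortality and the stated effect sizes. They apply to mortality. The mRS and CPC are ordinal (5.2), so a Hosmer-Lemeshow test for functional outcome needs a dichotomy that the protocol does not give, and the miss rate there may differ.

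A reader might also infer that the trial's main result is at risk. It is not: the survival comparison of cEEG with rEEG does not depend on this test. Severity is minor.

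**What to change.** In Protocol 11.4, or in the statistical analysis plan:

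- Delete the clause that gives the Hosmer-Lemeshow test the purpose of assuring calibration.
- Report a smoothed observed-versus-predicted curve with its 95% band, and the calibration intercept and slope corrected for optimism by bootstrap. The correction is needed because in the fitting data a logistic model has intercept 0 and slope 1 by construction.
- Set no pass/fail tolerance; at this sample size a 10-point rule would fail even a correct model.
- Allow a non-linear term (spline or quadratic, tested by likelihood ratio) for continuous predictors. A curve against predicted risk would not show an error at the extremes of a single predictor.
- If the Hosmer-Lemeshow p-value is still shown, state that p > 0.05 is not evidence of calibration.

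The cost is a little more analysis work and one or two degrees of freedom per continuous predictor. No new data, patients or visits are needed.
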